## PROTOCOL SUMMARY

**Title:** A Pilot Prospective, Randomized Controlled Trial Assessing the Clinical Impact of Integrated Pharmacogenetic Testing on Selected OASIS Metrics, Re-hospitalizations and Emergency Department visits

**Synopsis:** Patients meeting eligibility criteria will be randomized into two groups, one receiving pharmacogenetic testing and the other not receiving pharmacogenetic testing. In this open-label trial, a pharmacist will make medication therapy recommendations using YouScript® Personalized Prescribing System for patients who receive genetic testing and standard drug information resources per usual for patients who do not undergo pharmacogenetic testing.

Both groups will be followed for 60 days. The number of re-hospitalizations and emergency department (ED) visits will be recorded as well as time to first re-hospitalization and time to first ED visit. Select OASIS metrics (e.g. M1034, M1242, M1710, M1720, M1745, M2110) and depression using PHQ-2 will be evaluated and documented at time of admission to home health, at 30 days, and at 60 days for improvement in overall status, pain, confusion, anxiety, depression, disruptive behavior, and the need for assistance with activities of daily living (ADLs) and instrumental activities of daily living (IADLs). The number of falls will be collected as well as the proportion of YouScript® recommendations accepted by study pharmacist and passed on to clinicians and the proportion of recommendations accepted by clinicians.

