**Objectives:**

Primary:

- To assess the number of re-hospitalizations at 30 and 60 days post discharge with pharmacogenetic testing and YouScript® Personalized Prescribing System
- To assess the number of Emergency Department visits at 30 and 60 days post discharge with pharmacogenetic testing and YouScript® Personalized Prescribing system

Exploratory:

- To assess time to first re-hospitalization.
- To assess time to first Emergency Department visit.
- To assess the impact of genetic testing on overall status according to OASIS M1034 at 30 and 60 days post discharge.
- To assess the impact of genetic testing on frequency of pain according to OASIS M1242 at 30 and 60 days post discharge.
- To assess the impact of genetic testing on frequency of confusion according to OASIS M1710 at 30 and 60 days post discharge.
- To assess the impact of genetic testing on frequency of anxiety

according to OASIS M1720 at 30 and 60 days post discharge.

- To assess the impact of genetic testing on depression according to PHQ-2 at 30 and 60 days post discharge.
- To assess the impact of genetic testing on frequency of disruptive behavior according to OASIS M1745 at 30 and 60 days post discharge.
- To assess the impact of genetic testing on the frequency of ADL and IADL assistance according to OASIS M2110 at 30 and 60 days post discharge.
- To assess whether YouScript® testing decreases falls
- To assess the proportion of YouScript® Personalized Prescribing System recommendations accepted by the study pharmacist and passed on to clinicians.
- To assess the proportion of study pharmacist recommendations acted on by clinicians.

**Sample size** 100 patients (50 intervention, 50 controls)

**Population:** The study population consists of patients aged 65 and older who are currently enrolled in home health and are presently taking or initiating treatment with at least one oral form of medication with a significant drug-drug or drug-gene interaction as defined by FDA boxed warning, FDA cautionary labeling, clinical literature or a YouScript® algorithm-predicted significant effect.

Those meeting eligibility criteria will be prospectively enrolled in either the “tested” group and undergo YouScript® testing or “untested” group and not undergo YouScript® testing.

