#### **3.3.2 Enrollment/Baseline**

Any new data will be collected during regularly scheduled nursing visits. Principal investigator will review to verify that subjects continue to meet the eligibility criteria.

- Obtain and document consent from subject on study consent form
- Verify inclusion/exclusion criteria
- Obtain demographic information, medical history, medication history, alcohol, and tobacco use history
- Collect blood/urine/saliva/other specimen
- Record results of selected OASIS metrics and PHQ-2
- For those randomized to intervention:
  - Collect buccal swab for testing

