### **3.4 Randomization Procedures**

Prior to enrollment the treatment assignments were generated as a simple random sample, with 50 patients in each treatment arm. The randomization was carried out in R version 3.1.1 (Vienna, Austria).

Patients will be numbered chronologically by date of enrollment and each number has been randomized *a priori* to a treatment arm as stated above. Nurses are assigned patients based on coverage area and schedule. Only the PI will have access to the randomization list as to avoid any manipulation of patients to different treatment arms.

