## **7 STATISTICAL CONSIDERATIONS**

The statistical analysis will include the comparison of the YouScript® and control groups the primary and exploratory outcomes. Poisson regression will be used to compare the number of re-hospitalizations at 30 days, the number of re-hospitalizations at 60 days, the number of ED visits at 30 days, the number of ED visits at 60 days and the number of falls. The log-rank test will be used to compare the time to the first re-hospitalization and the time to the first ER visit. OASIS and PHQ-2 scores will be compared using the Wilcoxon rank sum test. The chi-squared test or the Fisher's exact test (as needed) will be used to compare the proportion of cases with acceptance by the study pharmacist and passing on to clinicians and the proportions of recommendations acted on by clinicians. Calculations will be carried out in R (Vienna, Austria). All tests will be two-sided.  $P < 0.05$  will be used to denote statistical significance. As the study is designed as a pilot, tests will not be adjusted for multiple comparisons.

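### The seven exploratory OASIS and PHQ-2 scales are compared without baseline adjustment, and the score to be tested is not defined, although admission values are scheduled in both arms

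*Combined protocol and SAP*

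**What the plan says.** Section 7 of the protocol, repeated word for word in the SAP extract, states: "OASIS and PHQ-2 scores will be compared using the Wilcoxon rank sum test". No covariate, change score or stratified version is named. The surrounding rules are "All tests will be two-sided", a threshold of P < 0.05 that "will be used to denote statistical significance", and "As the study is designed as a pilot, tests will not be adjusted for multiple comparisons".

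The admission values are part of the design. According to the Protocol Summary, the items "will be evaluated and documented at time of admission to home health, at 30 days, and at 60 days for improvement in overall status" and the other listed domains. Section 3.3.2 has this step at enrollment, for both arms: "Record results of selected OASIS metrics and PHQ-2". Section 5.1 schedules the same measures at admission, Day 30 and Day 60. The Appendix A footnote places the OASIS items at baseline as standard of care. The data entry form in Appendix C has an admission column for each of the seven scales.

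The sample is "100 patients (50 intervention, 50 controls"). Under Section 3.4, "treatment assignments were generated as a simple random sample, with 50 patients in each treatment arm", and no stratification is mentioned. Sections 2.1 and 2.2 list these scales among the exploratory outcomes, at 30 and 60 days. The amendments of March 24, 2016, made after study completion, revise the count models and leave this analysis as it was.

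**The concern.** The Protocol Summary frames these scales as measures of improvement, and the data needed to account for each patient's starting point are collected. Yet nothing in Section 7 brings the admission score into the comparison. If the follow-up score is what is tested, two things are lost. Variation between patients that was already present at admission stays in the error term. And if the arms happen to differ at admission, that difference is carried into the follow-up comparison, where it can look like an effect or hide one.

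The plan also leaves open which quantity is tested. A Wilcoxon test on Day 60 values and one on change from admission are different analyses with different power, and Section 7 fits either. With seven scales, two follow-up times, a 0.05 threshold for each test and no multiplicity adjustment, that is a choice to settle before the data are seen.

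**Working it through.** The documents give no power, SD, effect size or baseline-to-follow-up correlation for these scales, so there is no stated figure to reproduce. From the documents I take 50 per arm, unstratified allocation and a two-sided 0.05 level. I assume a half-SD effect and a correlation ρ of 0.3 to 0.7.

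**1. Chance imbalance at admission.** The standard error of the difference in baseline means is √(2/50) = 0.20 SD.
- P(gap > 0.2 SD) = 2[1 − Φ(0.2/0.20)] = 2[1 − Φ(1)] = 0.32.
- P(gap > 0.4 SD) = 2[1 − Φ(0.4/0.20)] = 2[1 − Φ(2)] = 0.046.
- If the seven scales were independent (an assumption), the chance that at least one exceeds 0.4 SD is 1 − 0.954⁷ ≈ 0.28.

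**2. Type I error of an unadjusted test, given a baseline gap b.** In the normal approximation the test statistic has mean ρb/0.20 and SD √(1 − ρ²).

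| Gap b | ρ = 0.3 | ρ = 0.5 | ρ = 0.7 |
|---|---|---|---|
| 0 | 0.040 | 0.024 | 0.006 |
| 0.2 SD | 0.050 | 0.048 | 0.039 |
| 0.4 SD | 0.081 | 0.134 | 0.216 |

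For example, at ρ = 0.5 and b = 0.4 the mean is 1.0 and the SD is 0.866, and 1 − Φ((1.96 − 1.0)/0.866) ≈ 0.134. Averaged over all gaps the error is 0.05. A gap of 0.2 SD does not inflate it at these correlations; a gap of 0.4 SD does.

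**3. Precision, continuous approximation.** Adjustment multiplies the variance by 1 − ρ². Power is Φ(0.5/(s × 0.20) − 1.96), with s = 1 unadjusted and s = √(1 − ρ²) adjusted.

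| ρ | 1 − ρ² | Equivalent n per arm, 50/(1 − ρ²) | Power unadjusted | Power adjusted |
|---|---|---|---|---|
| 0.3 | 0.91 | 55 | 0.705 | 0.746 |
| 0.5 | 0.75 | 67 | 0.705 | 0.823 |
| 0.7 | 0.51 | 98 | 0.705 | 0.938 |

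**4. Precision, ordinal simulation.** These are coarse scales, so the continuous figures flatter the gain. I simulated a latent bivariate normal variable cut into five levels (assumed 25, 20, 20, 25 and 10% of patients), with a half-SD latent shift, 50 per arm and 3,000 trials per setting.

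| ρ (latent) | Wilcoxon, follow-up | Wilcoxon, change | Rank ANCOVA |
|---|---|---|---|
| 0.3 | 0.645 | 0.459 | 0.677 |
| 0.5 | 0.637 | 0.552 | 0.718 |
| 0.7 | 0.619 | 0.731 | 0.835 |

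With no effect, all three tests rejected in 4.4 to 5.3% of trials at these correlations. A repeat of the simulation gave 63–65% for Wilcoxon on follow-up scores and 66, 75 and 85% for rank ANCOVA. The ranges are therefore about 62–65% against 66–68, 72–75 and 84–85%.

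**5. An item with a floor.** If 85% of patients score at the lowest level, which is conceivable for disruptive behavior (M1745), power for Wilcoxon against rank ANCOVA is 0.297 against 0.308 at ρ = 0.6, and 0.307 against 0.358 at ρ = 0.7. These are gains of 1 and 5 points. A repeat gave 0 to 4.

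**The case against.** The strongest defence is that nothing here is invalid. A rank sum test on randomized groups holds its overall level, as the simulation shows. The outcomes are exploratory, in a study that calls itself a pilot, and no power is claimed for them. All of that stands. A reader might infer that the plan inflates the false-positive rate; overall it does not. Inflation appears only conditionally on a sizeable baseline gap.

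Second, Section 7 says only scores, and the Protocol Summary speaks of improvement, so the baseline may enter through a change score. A reader should therefore not infer that admission data are certainly discarded. The objectives at 30 and 60 days fit follow-up values at least as well, so the ambiguity is itself part of the point. It does not rescue the analysis: in the simulation the change score is less powerful than rank ANCOVA at every correlation, and at 0.3 and 0.5 it is worse than ignoring the baseline.

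Third, the size can be overstated. It is tempting to say that admission differences dominate the error, but ρ² is 0.09, 0.25 and 0.49 at the assumed correlations, always under half. It is also tempting to call a serious imbalance likely, but for any one item a gap above 0.4 SD has a 4.6% chance. Some baselines will be unusable, because M1034 and M2110 allow UK and M1710 and M1720 allow NA.

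Section 2 mentions propensity score matching, which might seem to deal with imbalance. Section 7 carries it into no analysis.

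**Conclusion.** The point holds as a recommended improvement, not as an error of validity. Section 7 leaves the analysed score undefined and makes no adjustment for admission values that are scheduled in both arms. For an assumed half-SD effect on an item with patients spread over five levels, the cost is about 2 to 4 points of power at a correlation of 0.3, about 8 to 11 at 0.5, and just over 20 at 0.7. On floor-heavy items it is about 0 to 5 points. The direction does not depend on how the word scores is read; the size rests on a correlation, an effect and level distributions that the documents do not give.

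The primary outcomes are not touched. A reader might infer that the count models for re-hospitalizations and ED visits should likewise be adjusted for admission M1034. The documents do not support that step: M1034 is not the baseline of those counts, no association with them is shown, and none of the calculations above involves a count outcome.

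**What to change.** Replace the sentence in Section 7 with wording such as:

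> Each OASIS item and PHQ-2 will be compared between arms at Day 30 and at Day 60 by analysis of covariance on ranks, with arm as the factor and the patient's admission score on the same item as covariate. UK and NA codes will be treated as missing and will not be ranked. An unadjusted Wilcoxon rank sum test on the follow-up scores will be reported as a sensitivity analysis.

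This also settles which score is analysed. It needs minor programming and no new data. A few patients with an unusable admission code would drop out of the adjusted comparison; the report should give their number by arm and item, and the sensitivity analysis keeps those who have a usable follow-up score. Since the 2016 amendments were written after study completion, an adjusted analysis done now must be labelled post hoc and shown beside the planned test.

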## **8 RESULTS DISSEMINATION**

The study will be registered in the public trials registry *ClinicalTrials.gov*. After the results have been analyzed a manuscript will be submitted for publication within 1 year of the last patient being enrolled in the study.

## **9 APPENDICES**

- Appendix A: Schedule of procedures table
- Appendix B: Consent form
- Appendix C: Example Data Entry Form
- Appendix D: YouScript® Risk Analysis Tool

## APPENDIX A: SCHEDULE OF PROCEDURES

| Study-Specific Procedures                                                          | Screening | Baseline
(Day 0) | Follow-up
(Day 30) | Follow-up
(Day 60) |
|------------------------------------------------------------------------------------|-----------|---------------------|-----------------------|-----------------------|
| Signed Consent Form                                                                | X         |                     |                       |                       |
| Verification of Eligibility                                                        | X         |                     |                       |                       |
| YouScript® testing                                                                 |           | X                   |                       |                       |
| Assess OASIS M1034/Overall status*                                                 |           |                     | X*                    |                       |
| Assess OASIS M1242/Pain*                                                           |           |                     | X*                    |                       |
| Assess OASIS M1710/Confusion*                                                      |           |                     | X*                    |                       |
| Assess OASIS M1720/Anxiety*                                                        |           |                     | X*                    |                       |
| Assess PHQ-2/Depression*                                                           |           |                     | X*                    |                       |
| Assess OASIS M1745/Disruptive Behavior*                                            |           |                     | X*                    |                       |
| Assess OASIS M2110/Need for ADL & IADL Assistance*                                 |           |                     | X*                    |                       |
| Abstraction of data from patient chart regarding healthcare resource utilization** |           |                     | X                     | X                     |
| Survey of clinician regarding impact on clinical decision-making                   |           |                     | X                     | X                     |

*\*All OASIS indicators are assessed as part of standard of care at baseline and follow-up (Day 60).*

*Additionally, study participants will be assessed at 30 days for the indicated select OASIS indicators.*

*\*\*Falls will be assessed at Day 60; re-hospitalizations and ED visits at Day 30 and Day 60; time to 1st ED visit and re-hospitalization at time of occurrence.*

# APPENDIX C: Example Data Entry Form

| PATIENT | AGE | ETHNICITY | GENDER | M1034/Overall Status |        |        | M1242/Pain |        |        | M1710/Confusion |        |        | M1720/Anxiety |        |        | M1745/Behavior |        |        | M2110/ADL & IADL |        |        | PHQ2/Depression |        |        | Hospitalizations |             |             | ER Visits   |             |   |
|---------|-----|-----------|--------|----------------------|--------|--------|------------|--------|--------|-----------------|--------|--------|---------------|--------|--------|----------------|--------|--------|------------------|--------|--------|-----------------|--------|--------|------------------|-------------|-------------|-------------|-------------|---|
|         |     |           |        | Admit                | Day 30 | Day 60 | Admit      | Day 30 | Day 60 | Admit           | Day 30 | Day 60 | Admit         | Day 30 | Day 60 | Admit          | Day 30 | Day 60 | Admit            | Day 30 | Day 60 | Admit           | Day 30 | Day 60 | Time to 1st      | # at Day 30 | # at Day 60 | Time to 1st | # at Day 30 | # |
| 1       |     |           |        |                      |        |        |            |        |        |                 |        |        |               |        |        |                |        |        |                  |        |        |                 |        |        |                  |             |             |             |             |   |
| 2       |     |           |        |                      |        |        |            |        |        |                 |        |        |               |        |        |                |        |        |                  |        |        |                 |        |        |                  |             |             |             |             |   |
| 3       |     |           |        |                      |        |        |            |        |        |                 |        |        |               |        |        |                |        |        |                  |        |        |                 |        |        |                  |             |             |             |             |   |
| 4       |     |           |        |                      |        |        |            |        |        |                 |        |        |               |        |        |                |        |        |                  |        |        |                 |        |        |                  |             |             |             |             |   |
| 5       |     |           |        |                      |        |        |            |        |        |                 |        |        |               |        |        |                |        |        |                  |        |        |                 |        |        |                  |             |             |             |             |   |
| 6       |     |           |        |                      |        |        |            |        |        |                 |        |        |               |        |        |                |        |        |                  |        |        |                 |        |        |                  |             |             |             |             |   |
| 7       |     |           |        |                      |        |        |            |        |        |                 |        |        |               |        |        |                |        |        |                  |        |        |                 |        |        |                  |             |             |             |             |   |
| 8       |     |           |        |                      |        |        |            |        |        |                 |        |        |               |        |        |                |        |        |                  |        |        |                 |        |        |                  |             |             |             |             |   |
| 9       |     |           |        |                      |        |        |            |        |        |                 |        |        |               |        |        |                |        |        |                  |        |        |                 |        |        |                  |             |             |             |             |   |
| 10      |     |           |        |                      |        |        |            |        |        |                 |        |        |               |        |        |                |        |        |                  |        |        |                 |        |        |                  |             |             |             |             |   |
| 11      |     |           |        |                      |        |        |            |        |        |                 |        |        |               |        |        |                |        |        |                  |        |        |                 |        |        |                  |             |             |             |             |   |
| 12      |     |           |        |                      |        |        |            |        |        |                 |        |        |               |        |        |                |        |        |                  |        |        |                 |        |        |                  |             |             |             |             |   |
| 13      |     |           |        |                      |        |        |            |        |        |                 |        |        |               |        |        |                |        |        |                  |        |        |                 |        |        |                  |             |             |             |             |   |
| 14      |     |           |        |                      |        |        |            |        |        |                 |        |        |               |        |        |                |        |        |                  |        |        |                 |        |        |                  |             |             |             |             |   |
| 15      |     |           |        |                      |        |        |            |        |        |                 |        |        |               |        |        |                |        |        |                  |        |        |                 |        |        |                  |             |             |             |             |   |
| 16      |     |           |        |                      |        |        |            |        |        |                 |        |        |               |        |        |                |        |        |                  |        |        |                 |        |        |                  |             |             |             |             |   |
| 17      |     |           |        |                      |        |        |            |        |        |                 |        |        |               |        |        |                |        |        |                  |        |        |                 |        |        |                  |             |             |             |             |   |
| 18      |     |           |        |                      |        |        |            |        |        |                 |        |        |               |        |        |                |        |        |                  |        |        |                 |        |        |                  |             |             |             |             |   |
| 19      |     |           |        |                      |        |        |            |        |        |                 |        |        |               |        |        |                |        |        |                  |        |        |                 |        |        |                  |             |             |             |             |   |
| 20      |     |           |        |                      |        |        |            |        |        |                 |        |        |               |        |        |                |        |        |                  |        |        |                 |        |        |                  |             |             |             |             |   |

